### Inclusion and exclusion criteria

Each included clinic must be staffed by at least one paediatrician with an interest in diabetes, a diabetes specialist nurse and comprise of 40 or more potentially eligible children and adolescents. Eligibility criteria for participants are provided in Table 1.

**Table 1 T1:** Participant inclusion/exclusion criteria

Inclusion criteria	Exclusion criteria
1. Type 1 diabetes	1. Not under care of parent or guardian (i.e. a looked after child)
2. 4-15 years old	2. Co-morbid chronic illness likely to impact on HbA1c independent of patient's ability to manage diabetes (e.g. condition requiring steroid treatment, cystic fibrosis, renal failure)
3. Under care of paediatric/adolescent diabetes team for duration of trial	3. In receipt of ongoing psychiatric/psychological therapy at the start of the study
4. Diabetes diagnosed > 12 months earlier	4. Other patients judged by clinical carer to be vulnerable due to existing medical or social condition
5. Parental or carer (and child when able) consent given	
6. Ability of patient and at least one parent or carer to complete study materials (questionnaires)	

### Recruitment

Participating families are recruited by the research nurse and written informed consent obtained from a parent. Where appropriate written informed consent or assent is obtained from the child (N.B. both parent and patient must be in agreement to take part in the study). Recruitment and randomisation of clinics was undertaken in three blocks [37]: however, patients within each centre will be approached en-bloc by letter.

### Randomisation

Half of the trial centres will be randomised to the intervention arm, and half to the control arm. Teams were recruited and then randomisation optimally balanced [38] for population (patient list) size. After the first bock of randomisations, each subsequent block incorporates the balance from the previous allocation(s).

### Trial procedures

#### Intervention

Members of clinical teams allocated to the intervention arm will undergo a blended training programme comprising web-based material and face-to-face seminars (The Talking Diabetes Programme). The training course aims to prepare practitioners for constructive behaviour change conversations with patients and to provide practitioners with strategies and skills for encouraging behaviour change. The training emphasises the importance of shared agenda-setting, and drawing upon the Motivational Interviewing approach, emphasises the importance of a guiding style when consulting with patients about behaviour change. Practitioners work their way through a number of distinct programme parts with an approximate total duration of 1.5 hours (delivered via three main e-learning modules). In addition, more interactive web-based components of the course allow practitioners to record their thoughts and experiences as they proceed through the programme. Two face-to-face seminars (approximately 2 weeks apart) with combined clinical teams also form part of the training course. Time spent on off-line learning activities such as discussing the training content in pairs, is recorded online. Following the second face-to-face workshop, participants will be invited to submit reports of three consultations in which they use their newly acquired skills and feedback will be provided by pre-assigned trainers.

The training programme shows practitioners how to use a device (3T: TimeToTalk) for promoting shared agenda-setting during clinical encounters with patients. This consists of a rigid folder and an inserted paper agenda pad of tear-off sheets which can be completed in advance by patients and carers to record topics of importance to be raised within consultations. Practitioners have the option to complete a proforma on which general topics discussed at clinic visits can be recorded and kept with patient notes, to facilitate clinical record keeping and communication between healthcare professionals. Copies of the paper agenda-setting pad (without folder) have been made available to each clinic to refill or replace folders as required and for patients not otherwise recruited to the study.

#### Frequency & duration of follow-up

Patients are required to provide blood samples, and patients and carers to complete questionnaires immediately post-recruitment, following their first clinic visit during the trial phase, and at one year. Professionals have their competencies measured post training and after one year to assess acquisition and maintenance of new skills. Professionals also provide attitudinal self-rating (importance and confidence) at the start and end of the training programme and at one year.

#### Baseline data collection

Baseline data is collected by the research nurse either in clinic or the patient's home. The research nurse provides patients and carers with a copy of an age-appropriate questionnaire (7-10 yrs; 11-15 yrs) assessing quality of life outcomes, to be returned directly to the trial coordinating centre (who will also follow up non-responders). The research nurse will complete a baseline Case Report Form (CRF), recording demographic information and clinical data (taken from patient notes).

Blood samples are collected by research nurses and sent to a single UK laboratory (Diabetes Research Network Wales Laboratory, Llandough Hospital) for measurement of HbA1c concentrations. Results are reported directly to the research team, following adjustment against the Diabetes Control and Complications (DCCT) international standard. Where a sample is lost or spoilt in transit, the research nurse will approach the patient and carer for consent to provide a second sample. In the event that a patient HbA1c sample is in excess of 15.0% (considered to be indicative of a patient at significant acute clinical risk) local diabetes teams responsible for patient care will be informed so that comparison can be made with the most recent HbA1c sample taken and analysed locally. Any patient contact resulting from notification of a high HbA1c value is at the discretion of the patient's diabetes care team: the research team have no direct contact with patients in connection with HbA1c. GPs will be informed in writing of their patient's participation in the trial by the research nurse.

#### Data collection during the trial phase: CRF and Interim Questionnaire

Clinical patient details (HbA1c, height, weight, BMI, insulin regimen), health service contacts and patient borne costs are recorded by the local research nurse at each clinic visit on the CRF. The research nurse also records who patients consulted with, for how long, and whether patients consulted on their own at each visit. Patients and carers are also asked to complete an interim questionnaire (assessing patient enablement) at their first clinic visit following the start of the trial.

#### Follow-up data collection

Capillary HbA1c samples for patients, and questionnaires for patients and carers will be repeated at one year. Where possible, primary outcome data (HbA1c) will be collected two weeks either side of the expected date of follow-up (i.e. within a 1-month window). Follow-up questionnaires will be sent to patients and carers directly by the trial coordinating centre. Follow-up questionnaires will also assess preferences for care using a Discrete Choice Experiment (DCE) not previously included at baseline.

### Primary & secondary outcomes

#### Patient outcomes

Careful selection of outcome measures for children is important to ensure appropriateness, feasibility and acceptability. Measure selection has been informed by two HTA systematic reviews [5,39] and through consultation with the stakeholder reference group in the intervention development phase. Patient-reported outcomes (assessed via an age-appropriate questionnaire at baseline and follow-up) include measures of diabetes-specific quality of life [40-42], self-efficacy [43], patient enablement [44] and patient perceptions of the diabetes team [43,45] importance of, and confidence in their ability to undertake diabetes care and monitoring activities (patients aged 11+ only) and preferences for care (DCE: follow up only [46]). Biochemical and clinical measures for patients include HbA1c, BMI, insulin type, dose and number of injections and self-reported frequencies of moderate and severe hypoglycaemic episodes.

#### Carer outcomes

Carer outcomes include demographic information (age, gender, ethnic origin, socio-economic status), parent measures of quality of life, anxiety and perceptions of the diabetes team [43] including items relating to communication between practitioners, feelings towards the next visit and continuity of care [45], importance of, and confidence in their ability to undertake diabetes care and monitoring activities. Proxy outcomes (patients aged 4-11) comprise diabetes-specific quality of life [40] and self-care [41]. Patient and carer outcome measures are summarised in Table 2.

**Table 2 T2:** Patient and carer outcome measures

Outcome	Measure	Respondents
Diabetes-specific quality of life	Paediatric Quality of Life Inventory (PEDSQoL diabetes module: 11 items [40])	Patient (11+yrs), parent proxy (patients 5-11 yrs), parent
	Problem Areas in Diabetes (PAID: 23 items [41])	
	2 global items to assess change in QoL (follow-up only)*	

Perceptions of health care provider	Health Care Climate Questionnaire (HCC: adapted from 7 to 5-point scale [43])	Patient, parent
	3 additional items (respondents asked to circle an emotion to indicate anticipatory feelings towards going to clinic)*	
	Patient Enablement Inventory (PEI: 6 items [44])	
	Continuity of Care Scale (8 items [45])	

Self-efficacy	Perceived Competency Scale (4 items [43])	Patient, parent

Self-care	'Mis-management' (4 items adapted from Weisberg-Benchall et al. [42])	Patient (11+yrs), parent proxy (patients 5-11 yrs)
	Importance of self-care (6 items)* and confidence in ability (6 items)*	Patient, parent

*Indicates items created specifically for use in the current evaluation

#### Resource use

The cost of the intervention includes the cost of training intervention teams. The following training data will be recorded: travel costs to seminars, time spent on off-line learning activities (i.e. discussion of training content in pairs, reported on-line), time spent at seminars and time spent on-line (automatically recorded on website). Other training costs (e.g. venue, training materials) will also be calculated. Secondary costs are represented by between-group differences in service use including in-patient admissions (including ITU and HDU care), A&E attendances, clinic attendances, contacts with the diabetes team (home, telephone, face-to-face, electronic), other health service contacts (GP attendances, any other) and medication or equipment use (e.g. insulin type and dose). Patient-borne costs are also being assessed. These include travel to clinic, school absences and time taken off work by carers.

#### Process evaluation outcomes

Training outcomes for clinical teams will be evaluated and comprise behaviour change consultation competencies assessed via audio-recording of clinical sessions (post-training and at one year). Competencies for practitioners in the control group will be assessed at the end of the study period, prior to training [47]. Practitioners' confidence in, and importance of incorporating behaviour change into consultations will also be assessed (before and after training; one year after training); as will any systemic service changes at follow-up (e.g. timing of consultations).

### Analysis

#### Main analysis

The main analysis will be an intention to treat comparison of HbA1c values between the two groups of patients at one year. This will use multi-level modelling to allow for cluster (centre) and individual effects (including baseline concentrations of HbA1c as a covariate). Secondary analysis of other outcomes such as quality of life and cost will also be conducted using multi-level modelling incorporating baseline scores as covariates. A dose-response analysis will be conducted to explore associations between the amount of patient contact and an intervention effect. The two groups will also be compared on the non-attendance rate as the intervention may improve motivation to attend. A review of patient outcome measures used in diabetes, whilst predominantly in adults, concluded that whilst most have been shown to have content validity, there is less available evidence regarding reliability and responsiveness to change [48]. Responsiveness of the specific measures used will be assessed using both effect sizes and correlation to clinical variables and self-rated change.

Competence, confidence and importance of behaviour change counselling will be compared between the two groups at one year using a two level linear regression model controlling for profession. Short and long term impacts of the intervention will be analysed within the intervention group only using repeated measures ANOVA. Analysis of reliability of the competence inventory will be conducted on the trial data.

No formal subgroup analyses are planned. However, exploratory analysis of the impact of patient level factors (e.g. age and gender) and clinic level factors (e.g. size of clinic) on the effect of the intervention will be carried out. No interim analyses are planned.

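### Centre list size is balanced in the allocation but not named in the primary model; if it is prognostic, the treatment-effect standard error will be somewhat too large

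*Protocol article*

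**What the plan says.** Under Randomisation, allocation is 1:1 by centre ("Half of the trial centres will be randomised to the intervention arm, and half to the control arm"), and the method is described as follows: "Teams were recruited and then randomisation optimally balanced [38] for population (patient list) size". List size is the only balancing factor named. Under Recruitment: "Recruitment and randomisation of clinics was undertaken in three blocks". The Randomisation section adds that "each subsequent block incorporates the balance from the previous allocation(s", so balance is carried forward from block to block.

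Under Main analysis, the one-year HbA1c comparison is by intention to treat: "This will use multi-level modelling to allow for cluster (centre) and individual effects (including baseline concentrations of HbA1c as a covariate". Secondary patient outcomes use the same kind of model with baseline scores as covariates. The same section gives clinic size one role, as an example in an exploratory analysis of "clinic level factors (e.g. size of clinic) on the effect of the intervention will be carried out".

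**The concern.** Constrained allocation makes the arms more alike on the balancing variable than simple randomisation would. The treatment estimate is then less variable in repeated use of the design, provided that the variable is related to the outcome. A model that omits the variable does not register this gain. The centre differences due to list size stay in the estimated between-centre variance, and the standard error is calculated as though list size could still have differed between arms by chance.

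The result is confidence intervals wider than the design warrants, a true type I error below the nominal 5%, and some lost power. With 26 centres, the number of centres and the variance between them have a large influence on precision, so an avoidable loss at that level is worth removing. It is a matter of efficiency and of matching the analysis to the allocation, not of validity.

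**Working it through.** **Inputs from the protocol article (Sample size; Design).** ICC 0.08 from the Welsh audit; effect size 0.4; 80% power; 5% significance; 24 centres of 23 in the calculation; 700 patients to be recruited with 78% follow-up; 26 centres taking part.

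**The plan's own figure.**
- Individually randomised: 99 per arm, 198 in total (stated 200).
- Design effect: 1 + (23 − 1) × 0.08 = 2.76, and 200 × 2.76 = 552 (stated 550).
- Loss to follow-up: 550 / 0.78 = 705 (stated 700).

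The sample size reproduces and does not depend on the present point.

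**Assumed, because the documents do not give it.** The share R² of between-centre variance explained by list size: 0, 10%, 20% and 40%. The ICC after conditioning on individual baseline HbA1c: 0.04 and 0.02, alongside the audit value of 0.08, for which no baseline adjustment is mentioned.

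**Formula.** Analysed patients per centre: 700 × 0.78 / 26 = 21. The variance of a centre mean is proportional to ICC + (1 − ICC)/21. If balancing removes the list-size part from the arm contrast, then

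ratio of true to reported SE = √{ [ICC(1 − R²) + (1 − ICC)/21] / [ICC + (1 − ICC)/21] }

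and the SE excess is 1/ratio − 1.

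For ICC 0.08 and R² = 0.1, (1 − 0.08)/21 = 0.0438. The ratio is √(0.1158/0.1238) = 0.967, and the excess is 3.4%.

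| R² | ICC 0.08: ratio, excess | ICC 0.04: ratio, excess | ICC 0.02: ratio, excess |
|---|---|---|---|
| 0 | 1, 0% | 1, 0% | 1, 0% |
| 0.10 | 0.967, 3.4% | 0.976, 2.4% | 0.985, 1.5% |
| 0.20 | 0.933, 7.2% | 0.952, 5.0% | 0.970, 3.1% |
| 0.40 | 0.861, 16.1% | 0.902, 10.9% | 0.938, 6.6% |

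**Type I error.** With 26 − 2 = 24 degrees of freedom throughout, the true level of a nominal 5% test is 2 × P(t₂₄ > 2.064/ratio). At ICC 0.08 this gives 4.3%, 3.7% and 2.5% for R² of 10%, 20% and 40%, and 5.0% at zero.

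**Check by simulation.** 4,000 trials per scenario were analysed at centre level. The assumptions were ICC 0.08, about 21 patients per centre, blocks of 8, 8 and 10 centres, and allocation drawn from the best-balanced tenth of arrangements in each block with carry-over. The standard errors are for the model without list size; power is for an effect of 0.4 SD.

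| R² for list size | True SD of estimate | Mean reported SE | Type I error | Power without list size | Power with list size |
|---|---|---|---|---|---|
| 0 | 0.138 | 0.138 | 5.0% | 79.6% | 79.6% |
| 0.10 | 0.135 | 0.139 | 4.4% | 78.6% | 80.8% |
| 0.25 | 0.125 | 0.139 | 3.1% | 82.0% | 85.9% |
| 0.50 | 0.112 | 0.140 | 1.6% | 82.4% | 91.9% |

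The SE excesses are about 3%, 11% and 24% at shares of 10%, 25% and 50%, close to the formula (3%, 9% and 22%). Adding list size brought the reported SE back to the true SD and type I error to about 5%. The test was not anti-conservative in any scenario.

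With block explaining 10% of between-centre variance and list size none, type I error was 4.1% unadjusted and 4.8% with both terms in the model. With neither prognostic, fitting both gave 79.3% power against 79.6% without them.

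**The case against.** The strongest objection is that the text does not exclude list size. The covariate statement is introduced as an inclusion, not as a complete list. This is a condensed article, and the SAP, which may add centre-level terms, is not shown. That stands: a reader might infer that the trial will certainly analyse without list size, and the documents do not establish that. What remains is that the article does give clinic size a place in its analysis section, and that place is exploratory.

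A reader might also infer that the stated standard errors are wrong as a matter of fact. They are wrong only if list size predicts one-year HbA1c given baseline, and the document gives no evidence either way. At a zero share the model as described is correct.

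The magnitude at ICC 0.08 is an upper version. Individual baseline HbA1c may absorb much of any stable difference between centres, including any linked to clinic size. At 0.08 the between-centre part is 0.08/0.1238 = 65% of the variance of a centre mean; at 0.02 it is 0.02/0.0667 = 30%, so whether it dominates precision depends on an ICC that is not given. The formula also takes the balancing as complete, and how tightly allocation was constrained depends on a cited method not available here.

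Finally, a reader might put block on the same footing as list size. The article names only list size as a balancing factor, describes balance carried forward across blocks rather than balance within each block, and says nothing about calendar or season effects on HbA1c. The case for block is weaker.

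**Conclusion.** The point holds for list size in a conditional and modest form. The allocation is constrained on a centre-level variable that the described primary model does not name. If that variable explains 10% to 40% of between-centre variance, the standard error is about 3% to 16% too large at ICC 0.08, about 2% to 11% at 0.04 and about 1.5% to 7% at 0.02. If it explains none, nothing is lost. The shares and the two lower ICCs are assumptions. The direction does not depend on them: any error makes the test conservative, with no bias and no excess of false positives. It would be wrong to read this as a threat to the trial's validity. It is a nearly free gain in efficiency and alignment.

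**What to change.** State the primary model as one-year HbA1c on arm, individual baseline HbA1c and centre list size (continuous, as used in the balancing) as fixed effects, with centre as a random effect. Use the same centre-level term for the patient-level secondary outcomes. If the SAP already does this, a sentence saying so is enough. Randomisation block may be added as a further fixed effect; whichever choice is made should be set down before the outcome data are seen, so that adjusted and unadjusted results cannot be chosen between afterwards.

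The cost is one sentence and one centre-level degree of freedom (24 to 23; critical t 2.064 to 2.069), or three with block (21; 2.080). The trial already holds both variables, and the planned sample size does not change.

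### Within-arm change in practitioner outcomes is analysed by repeated measures ANOVA with no team term, and for competence that contrast can show retention but not acquisition

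*Protocol article*

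**What the plan says.** The second paragraph under Main analysis in the protocol article plans two analyses of practitioner outcomes.

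- **Between arms.** Competence, confidence and importance "will be compared between the two groups at one year using a two level linear regression model controlling for profession".
- **Within the intervention arm.** "Short and long term impacts of the intervention will be analysed within the intervention group only using repeated measures ANOVA". The outcomes are not repeated in this sentence. From its position, I read it as covering the same three.

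The measurement schedule differs by outcome:

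- **Competence, intervention arm.** Process evaluation outcomes lists "behaviour change consultation competencies assessed via audio-recording of clinical sessions (post-training and at one year"). The Discussion gives the same two occasions.
- **Competence, control arm.** "Competencies for practitioners in the control group will be assessed at the end of the study period, prior to training".
- **Confidence and importance.** "Professionals also provide attitudinal self-rating (importance and confidence) at the start and end of the training programme and at one year".

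On the purpose of the competence measurements, Frequency & duration of follow-up says: "Professionals have their competencies measured post training and after one year to assess acquisition and maintenance of new skills".

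**The concern.** There are two separate problems with the within-arm analysis.

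**Clustering.** Design and Randomisation put half of 26 teams, so 13, in the intervention arm. Under Intervention, staff attend seminars as clinical teams and discuss the material in pairs. Gains and losses in skill may therefore be shared within a team. The between-arm model has a second level for this kind of dependence, whereas the within-arm ANOVA, as named, treats practitioners as independent.

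**What the competence contrast estimates.** With the first recording made after training, the within-arm contrast starts from the trained state. It can show whether skill was kept or lost over the year. It cannot show that skill was acquired.

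The article itself makes this analysis matter: skill retention is an aim of the process evaluation (The current trial), and the Discussion singles out skill maintenance as perhaps the leading challenge. Within the intervention arm, this ANOVA is the only stated analysis of change from post-training to one year. An understated standard error could produce a false finding of decay, or a more precise reassurance of maintenance than the data support. Either would colour the explanation of the HbA1c result. A flat competence profile might also be reported as an effect of training when it is only stability after training.

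**Working it through.** **The plan's own figures.** The article gives no sample size, ICC or precision for practitioner outcomes. Its ICC of 0.08 is for patient HbA1c and cannot be carried over. The patient calculation reproduces: 1 + (23 − 1) × 0.08 = 2.76, and 200 × 2.76 = 552 against the stated 550. It has no bearing on this point.

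**Step 1. What the schedule allows.**

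| Outcome | Before training | After training | One year | Control teams |
|---|---|---|---|---|
| Competence | none | yes | yes | once, at study end, untrained |
| Confidence, importance | yes | yes | yes | in the one-year comparison |

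For competence, the only within-arm contrast is one year minus post-training, which is retention. For confidence and importance, a short-term (before to after) and a long-term contrast both exist, though neither is controlled.

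**Step 2. Effect of ignoring team.** With two occasions, repeated measures ANOVA is equivalent to a one-sample t test on the change scores. Write the change for practitioner i in team j as d = δ + u_j + e_ij, with total variance σ², ICC of change ρ, m practitioners per team and N = 13m.

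- True variance of the mean change: (σ²/N) × [1 + (m − 1)ρ].
- Variance used by the ANOVA: about σ²/N.
- The standard error is therefore understated by a factor of √DE, where DE = 1 + (m − 1)ρ.

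Stable differences in level between teams cancel in d, so only shared change contributes to ρ.

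**Step 3. Numbers.** The inputs m = 3, 5, 8 and ρ = 0 to 0.20 are assumptions. Simulated type I error at nominal 5%, with 13 teams and 40,000 runs per cell:

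| Staff per team | ρ = 0 | ρ = 0.05 | ρ = 0.10 | ρ = 0.20 |
|---|---|---|---|---|
| 3 | 4.9% | 6.3% | 7.3% | 9.7% |
| 5 | 4.9% | 7.4% | 9.8% | 14.4% |
| 8 | 5.1% | 9.2% | 13.6% | 20.9% |

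Hand check at the two extremes, using 2Φ(−1.96/√DE):

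- m = 3, ρ = 0.05: DE = 1 + 2 × 0.05 = 1.10; 1.96/1.05 = 1.87; about 6.2%.
- m = 8, ρ = 0.20: DE = 1 + 7 × 0.20 = 2.40; 1.96/1.55 = 1.27; about 20.6%.

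Both agree with the simulation. The correct standard error is 1.05 to 1.55 times the one the ANOVA would report over this range. With ρ = 0 the ANOVA is sound.

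**The case against.** The strongest reply is that the ANOVA is a supplement. A reader might infer from it that the trial has no valid test of the training effect on practitioners. The article does not support that. The preceding sentence plans a randomised comparison at one year, "using a two level linear regression model controlling for profession", and control staff are still untrained when their competence is recorded. That comparison can speak to acquisition of competence as it stands at one year. The article does not say that the second level is the team, but that is the natural reading.

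Three other stronger readings also fail:

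- **That nothing was measured before training.** This is true of competence only. Confidence and importance are rated at the start of the programme.
- **That the p-values are certainly too small.** A within-practitioner contrast already removes stable team differences. Inflation needs correlated change, and the article gives no figure for it.
- **That practitioners who miss an occasion will be dropped.** The article does not say how missing occasions are handled. An analysis plan that is not shown may cover it, so this is not part of the point.

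What stands against the objection is that the article names the within-arm method, so it is not a detail left to a later plan. The between-arm comparison estimates a difference at one year, not change since training, and so does not replace the within-arm analysis. There is also a gap that wording cannot close: immediate post-training competence has neither an earlier measure nor a concurrent control. Setting it against control recordings made at study end would compare different times and should not be presented as a contemporaneous randomised contrast.

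**Conclusion.** The point holds in limited form. The stated within-arm ANOVA has no team term for practitioners in 13 teams, in contrast to the model named just before it. Its type I error may be about 6% to 21% at a nominal 5%, assuming 3 to 8 staff per team and an ICC of change of 0.05 to 0.20; it stays at about 5% if that ICC is 0. The size is therefore illustrative, while the inconsistency in method is on the page.

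For competence alone, the within-arm contrast estimates retention or decay and cannot support the acquisition purpose given under Frequency & duration of follow-up. These are process-evaluation outcomes. The HbA1c analysis, which models centre, is not affected.

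**What to change.** 1. Replace the repeated measures ANOVA with a mixed model for occasion within practitioner within team, using all available measurements. The team level should let change differ between teams (a random team-by-occasion effect). A random team intercept alone would not help, because it absorbs only the stable differences that the time contrast already removes. With 13 teams, use a small-sample degrees-of-freedom correction. In a balanced two-occasion layout the analysis reduces to a t test on 13 team mean changes, with 13 − 1 = 12 degrees of freedom.
2. Label the post-training to one-year competence contrast as retention only. Describe the confidence and importance contrasts as uncontrolled change from before training.
3. Reword the purpose given under Frequency & duration of follow-up so that any statement about acquisition of competence rests on the planned randomised one-year comparison with untrained control teams. State that the second level of that model is the team.

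No new data are needed. The cost is a few more lines of analysis text, and intervals that widen only as far as change is in fact shared within teams.
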